### Randomization, sequence allocation & allocation concealment{16a,b,c}

Simple randomization. All the eligible participants will be randomly assigned (in 1:1 ratio) in each arm to ensure balanced distribution between KSK and CZ arms. Randomization will be implemented by independent statistician who will not involve in data analysis. Equal numbers of cards with each arm assignment number randomly generated by computer will be placed in sequentially numbered envelopes that will be opened on patient enrolling.

### Blinding (masking){17a,b}

- No blinding.

### Specimen collection details {18a}

Appropriate clinical sample will be collected by laboratory personnel/ health care worker trained in specimen collection in presence of a clinician by following all biosafety precautions and using personal protective equipment (PPEs), clinical samples will be sent to the designated laboratory (ICMR empanelled) by following standard triple packaging.

Table 3: Sample collection details

| Specimen type                         | Collection materials                                       | Transport to Laboratory | Storage till testing          |
|---------------------------------------|------------------------------------------------------------|-------------------------|-------------------------------|
| Nasopharyngeal and oropharyngeal swab | Dacron or polyester flocced swabs*                         | 4 °C                    | ≤5 days: 4 °C >5 days: -70 °C |
| Serum                                 | Serum separator tubes (adults: collect 3-5 ml whole blood) | 4 °C                    | ≤5 days: 4 °C >5 days: -70 °C |

\*For transport of samples for viral detection, VTM (viral transport medium) will be used

### Specimen labelling and processing

Personal protective equipment (apron, hand gloves, face shield, N95 Masks etc.) will be used and all biosafety precautions will be followed so as to protect individuals and the environment. Proper labelling (name/age/gender/specimen ID) will be done on specimen container and other details of sender (name/address/phone number) on the outer container by mentioning “KSK\_COVID\_trial”

[figure not shown]

Figure 1: Lab Specimen collection

Laboratory sample collection Schedule: (i) Oropharyngeal swabs (0,7,14 days) - for SARS-CoV-2 RT-PCR (samples will be transported to Laboratory, as per the guidelines); (ii) Blood sample (0,7,14 days) (iii) ECG, Xray (Base line)

All samples would be stored for future-related tests.

Table 4: Schedule of investigations

| Parameter              | D0 | D7 | D14 |
|------------------------|----|----|-----|
| Haemogram\$            | ✓  | ✓  | ✓   |
| *LFT                   | ✓  |    | ✓   |
| #RFT                   | ✓  |    | ✓   |
| HbA1c, BS              | ✓  |    |     |
| qRT- PCR for SARS Cov2 | ✓  | ✓  | ✓   |
| Electrolytes           | ✓  | ✓  | ✓   |
| Chest X-ray            | ✓  |    |     |
| ECG                    | ✓  |    | ✓   |
| Immunoglobulins        | ✓  | ✓  | ✓   |

\$Hb%, total leucocyte count and differential WBC -neutrophils, lymphocytes, eosinophils, monocytes and basophils, RBC count, platelet count; #Renal function test -BUN, Creatinine; \*Liver function test -albumin, bilirubin, ALT, AST, alkaline phosphatase. AST, aspartate transaminase; ALT, alanine aminotransferase; RBC, red blood cell; WBC, white blood cell; BUN, blood urea nitrogen; ECG, electrocardiogram; SARS-CoV-2, severe acute respiratory syndrome coronavirus 2; qRT-PCR, real-time reverse transcription-polymerase chain reaction; HbA1c, haemoglobin A1c; Hb, haemoglobin

Frequency and duration of monitoring: (i) Patients will be monitored daily until discharge from the hospital and followed up till 14 days;

### Outcome assessment

Clinical outcomes: (i) Assessment of clinical symptoms (ii) Clinical profile of SSM (iii) Time to test COVID-19 Negative

Safety Assessment: (i) Elevation of ALT to more than five-fold upper normal limit; (ii) Anaphylaxis; and (iii) Adverse events and serious adverse events.

Laboratory outcomes: (i) Viral RNA loads and cycle threshold values in serial samples of nasopharyngeal

and oropharyngeal swabs and blood, collected every week (to document anti-viral activity). (ii) Immunoglobulins values in serial samples of serum collected every week (to document immunomodulatory effect)

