### Interventions Arm -1{11a}

#### **Kabasura Kudineer (Siddha Polyherbal decoction)**

Table 1: Composition of KSK

| S. No | Botanical name                 | Family         | Part Used   | Parts  |
|-------|--------------------------------|----------------|-------------|--------|
| 1.    | Zingiber officinale     | Zingiberaceae  | Rhizome     | 1 part |
| 2.    | Piper longum            | Piperaceae     | Fruit       | 1 part |
| 3.    | Syzygium aromaticum     | Myrtaceae      | Flower bud  | 1 part |
| 4.    | Anacyclus pyrethrum     | Asteraceae     | Rhizome     | 1 part |
| 5.    | Tragia involucrata      | Euphorbiaceae  | Leaves      | 1 part |
| 6.    | Solanum anguivi         | Solanaceae     | Leaves      | 1 part |
| 7.    | Terminalia chebula      | Combretaceae   | Fruit rind  | 1 part |
| 8.    | Justicia adathoda       | Acanthaceae    | Leaves      | 1 part |
| 9.    | Anisochilus carnosus    | Lamiaceae      | Whole plant | 1 part |
| 10.   | Costus speciosus        | Costaceae      | Rhizome     | 1 part |
| 11.   | Tinospora cordifolia    | Menispermaceae | Whole plant | 1 part |
| 12.   | Clerodendrum serratum   | Verbanaceae    | Leaves      | 1 part |
| 13.   | Andrographis paniculata | Acanthaceae    | Whole plant | 1 part |
| 14.   | Cyperus rotundus        | Cyperaceae     | Rhizome     | 1 part |
| 15.   | Sida acuta              | Malvaceae      | Whole plant | 1 part |

**SOP for preparation:** To 5g of KSK coarse powder, add 240 ml of water and allowed to boil till, it reduces to one-fourth (60ml) and filter the decoction (KSK).

**Dose** : 30 – 60 ml twice daily.  
**Dosage form** : Kudineer (decoction).  
**Route of administration** : Oral.  
**Time of administration** : twice a day- Morning and Night before food  
**Duration of therapy** : 14 days  
**Follow up period** : 14 days after treatment

[illegible]

|                    |  |   |   |   |   |   |   |   |   |   |   |   |   |   |   |   |
|--------------------|--|---|---|---|---|---|---|---|---|---|---|---|---|---|---|---|
| SSM principles     |  | ✓ | ✓ | ✓ | ✓ | ✓ | ✓ | ✓ | ✓ | ✓ | ✓ | ✓ | ✓ | ✓ | ✓ | ✓ |
| Laboratory Markers |  | ✓ |   |   |   |   |   | ✓ |   |   |   |   |   |   |   | ✓ |

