### Sample size {14}

As there is no prior work on this research question, so no assumptions for the sample size calculation could be made. The present study will serve as a pilot trial. We intend to study 60 patients, each 30 in two groups.

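### The ALT safety outcome is scheduled after baseline only at D14, the end of dosing; a promptly read ALT on the existing D7 blood would be a cheap improvement

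*Protocol*

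**What the plan says.** Under Outcome assessment, the first of the protocol's three safety items is "Elevation of ALT to more than five-fold upper normal limit". The footnote to Table 4 places ALT in the liver panel: "Liver function test -albumin, bilirubin, ALT, AST, alkaline phosphatase". Table 4 ticks that panel at D0 and D14 and leaves D7 blank.

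The KSK arm takes the decoction "twice a day- Morning and Night before food" for 14 days. The sampling schedule under Specimen labelling and processing gives "Blood sample (0,7,14 days", and Table 4 runs the haemogram, electrolytes and immunoglobulins at D7. Outcome assessment confirms that serum for immunoglobulins is taken weekly.

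Three other statements bear on the point:

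- Clinical monitoring: "Patients will be monitored daily until discharge from the hospital and followed up till 14 days".
- Retention of samples: "All samples would be stored for future-related tests".
- Sample size: "We intend to study 60 patients, each 30 in two groups".

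**The concern.** A liver threshold is most useful while the product can still be withdrawn. Here the sponsor has named the threshold, but its only planned measurement after baseline comes when the course is finishing. Participants are symptom-free at entry, and the test product is a 15-ingredient decoction given at 30 to 60 ml twice daily. Daily observation can pick up a patient who becomes unwell and can prompt an unplanned test. It cannot pick up a rise in ALT without symptoms. Such a rise would run through the rest of the course unseen by scheduled testing, and if it resolved before D14 the planned tests would not record it either.

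At stake is a modest protection for participants, not the validity of the trial's comparison.

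**Working it through.** The protocol gives no figure to reproduce on this point. The check sets the schedule against the outcome and then counts doses and assays.

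**Inputs from the protocol**

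- Safety threshold: ALT above five times the upper limit (Outcome assessment).
- Liver panel, including ALT: D0 and D14 (Table 4 and footnote).
- Blood draws: D0, D7, D14 (Specimen labelling and processing).
- KSK dosing: twice daily for 14 days (Interventions Arm -1).
- Patients: 60, 30 per arm (Sample size).

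**Input assumed**

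- Time from D7 draw to result, t days. The protocol states none, so a range is shown.

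**Step 1: scheduled ALT results.** Now there are two, at D0 and D14: one after baseline, and none during the course in time to act. With a D7 tick there are two after baseline, one of them at mid-course. The longest interval between scheduled ALT tests falls from 14 to 7 days.

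**Step 2: KSK doses that could still be withheld.** Total doses = 2 × 14 = 28. Taking D7 as the midpoint, doses left when the result arrives = 2 × (7 − t).

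| Turnaround t (days) | Doses left | Share of 28 |
|---|---|---|
| 1 | 12 | 43% |
| 2 | 10 | 36% |
| 3 | 8 | 29% |
| 5 | 4 | 14% |
| 6 | 2 | 7% |
| 7 | 0 | 0% |
| Present schedule (D14 only) | 0 | 0% |

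Whether the first dosing day is called D0 or D1, and whether blood is taken before or after that day's doses, moves these counts by at most one day's dosing (2 doses). The count is for KSK only, because the description of the other arm's regimen is not legible in the copy at hand.

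**Step 3: is prompt testing assured?** It is not. Table 3 allows serum to wait at 4 °C for up to 5 days and at −70 °C beyond that. By the table above, a wait of 5 days leaves 4 doses and a wait of 7 leaves none. A tick at D7 alone does not secure the benefit; a time limit on the assay is needed as well.

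**Step 4: cost.** 60 patients × 1 assay = 60 assays, with no added draws. Table 3 gives the tube as "Serum separator tubes (adults: collect 3-5 ml whole blood" but does not say whether that volume also covers ALT.

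The number of additional patients who would be detected is not estimated. The protocol gives no event rate, onset time or duration for ALT rises, so any such figure would rest wholly on assumption.

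**The case against.** The strongest reply is that nothing here is an error. The outcome is defined and has a baseline and a later value. The liver panel, renal panel and ECG share a consistent D0/D14 pattern, and weekly values are promised only for viral load and immunoglobulins. ALT has no row of its own in Table 5, so no stated analysis needs a D7 value. The threshold is listed as an outcome, not as a stopping rule. Patients are 18 to 55 years old, those with comorbid conditions are excluded, physicians of both systems examine them, and a data safety monitoring committee is named.

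Most of that stands, and it limits the point to a design improvement of low severity. It does not remove it. Table 4 fixes the visit schedule, so this is not detail left for an analysis plan, and no later plan could produce a result in time to stop dosing. Examination and daily monitoring address symptoms, not a silent rise. Stored samples may allow a later count but no action at the time.

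A second reply is that part of the copy is illegible. At the end of the Interventions section, a fragment of a schedule has a Laboratory Markers row with three ticks, one of them mid-course. The row names no test and its headings are lost, so it neither shows nor excludes ALT at D7. Table 4 is specific and leaves that cell blank. The lost text might hold safety or discontinuation rules, so the claim here is confined to scheduled testing.

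A reader might go further and infer three things that the document does not support:

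- That the protocol contradicts itself. It does not; the D0/D14 schedule is consistent with everything else stated.
- That the comparison between arms is biased. Both arms share the schedule.
- That liver injury could not be found at all during dosing. An unscheduled test prompted by symptoms remains possible.

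**Conclusion.** The point holds as a cheap, low-severity improvement. It is certain from the protocol that no scheduled ALT result is available while KSK could still be stopped, although ALT is a named safety outcome and blood is taken at D7. The gain is one on-treatment result per patient. Its practical worth depends on turnaround, which is assumed: 12 to 10 doses of 28 could be withheld with a result in 1 to 2 days, falling to none at 7 days. It also depends on someone acting on the result. The documents give no basis for saying how often such rises would occur or that the event count would change materially.

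**What to change.** - In Table 4, tick the liver panel, or at least ALT, at D7 in both arms and run it on the blood already drawn that day.
- Require the assay to be done promptly and not batched from stored serum, for example with the result available within 1 to 2 days of the draw. Dosing need not be held meanwhile.
- Have a trial physician review each result on receipt and stop the study treatment if ALT exceeds the protocol's own five-fold limit. The trial is open-label, so this review threatens no blind.

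The cost is about 60 additional assays (30 per arm), prompt processing and physician review, and possibly a slightly larger tube volume at the same draw. No extra visit or venepuncture is needed.

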## Rationale: {6b}

In this context, one of the classical formulations from Siddha system of medicine is *Kabasura kudineer* (KSK) consists of 15 herbals ingredients which individually has anti-viral activity (6). Cucurbitacin B (-112.09), Cardiolipide (-111.5), Apigenin (-98.84) and Pyrethrin (-92.98) presented in the KSK were found to be effective in preventing novel corona virus binding and replication.(7) Determination of organoleptic characters, preliminary phytochemical analysis, physico- chemical analysis, TLC photo documentation and HPTLC fingerprint studies on KSK were analyzed.(8) Toxicological study on KSK showed that it is safe(9). KSK also possess anti pyretic, anti-inflammatory and anti-bacterial effect. Vitamin c and zinc supplementation(CZ) is being prescribed for the COVID19 positive asymptomatic patients admitted in isolation ward. The role of CZ in the management of COVID19 is still not clear. Therefore, we propose to compare the effect of KSK and CZ in terms of negative conversion of SARS CoV- 2 infection.

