## Objectives

### Primary:{7a}

- To determine efficacy of KSK compared with CZ in reducing the onset of clinical symptoms in asymptomatic patients
- To determine effectiveness of KSK compared with CZ in terms of reduction of SARS-CoV-2 viral load from the baseline
- To examine the effect of KSK compared with CZ on immune system in terms of selected immunological markers

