### Data Analysis plan {20}

The analysis plan on the primary and secondary outcome is described in the below table

Table 5: Statistical analysis plan{20a}

| Outcome                                                              | Hypothesis                                 | Outcome measure                                        | Methods of analysis            |
|----------------------------------------------------------------------|--------------------------------------------|--------------------------------------------------------|--------------------------------|
| Primary                                                       |                                            |                                                        |                                |
| Viral load of SARS-CoV-2                                             | Reduction of Viral Load after intervention | Viral Load                                             | T test                         |
| Immunological markers                                                | Improvement                                | Th1, Th2 cells                                         | T test                         |
| Secondary                                                     |                                            |                                                        |                                |
| Reduction in the risk of disease progression                         | Reduction of complication                  | Incidence of complication                              | Kaplan Meier survival analysis |
| Reduction in intensive supportive care and long-term hospitalization | Reduction of complication                  | Incidence of complication                              | Kaplan Meier survival analysis |
| Clinical profile in terms of Siddha System of Medicine (SSM)         |                                            | Questionnaire                                          | Chi-square test                |
| Adverse events/effects                                               |                                            | Presence of drug related adverse event (time to event) | Kaplan Meier survival analysis |

**Data monitoring {21a}:** The data safety monitoring committee constituted by Ministry of AYUSH will be responsible for the monitoring the data

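### Table 5 fixes a plain t test for the primary viral-load outcome, which cannot represent the PCR-negative results the protocol expects; a real KSK-CZ difference is then distorted, usually toward zero

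*Protocol*

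**What the plan says.** The second primary objective compares KSK with CZ "in terms of reduction of SARS-CoV-2 viral load from the baseline". Table 5 in the Data Analysis plan {20} carries this forward with the hypothesis "Reduction of Viral Load after intervention", viral load as the outcome measure and a t test as the method. The row names no scale and no time point, and it does not mention the cycle threshold (Ct). Ct appears only in Outcome assessment, where the laboratory outcomes begin "Viral RNA loads and cycle threshold values in serial samples of nasopharyngeal".

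Three other places show that negative results are expected:

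- The Rationale says the trial is meant to "compare the effect of KSK and CZ in terms of negative conversion of SARS CoV- 2 infection".
- The sampling schedule has "Oropharyngeal swabs (0,7,14 days) - for SARS-CoV-2 RT-PCR".
- Outcome assessment lists "Time to test COVID-19 Negative" as a clinical outcome. It has no row in Table 5.

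Every participant is laboratory confirmed at entry, so undetectable values should arise mainly after day 0. The Sample size section sets 30 patients per arm, calls the trial a pilot and gives no load distribution, SD or target difference.

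**The concern.** A PCR-negative sample has no Ct and no quantified load. It says only that the load is below what the assay can detect. Suppose, for illustration, a limit of 10^2. A patient who goes from 10^6 to 10^4 has a measured fall of 2 log10. A patient who goes from 10^4 to undetectable has fallen by at least 2 log10, but by how much more is unknown. A t test needs one number per patient and has no way to enter *at least*. The second patient must be left out or given a chosen number, and taking logs does not remove the difficulty.

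If KSK works, more of its patients will be in that position. The better arm then loses more of its information, and the estimated difference depends on the coding as well as on the treatment. Pilot estimates are commonly carried into the design of a later trial, so a distorted difference would matter beyond this one.

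**Working it through.** The protocol has no figure to reproduce: 60 patients is stated without a calculation. The check asks what a t test returns when the true difference is known.

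**Inputs.** From the protocol: 30 per arm, 1:1. Assumed, because the protocol gives none of them: follow-up log10 load normal with SD s = 1.5 in each arm, detection limit L = 2, true KSK-CZ difference 1.0, two-sided 5% test. The share of CZ patients who are negative is varied.

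**Formulas.** For an arm with mean m, let z = (m - L)/s.

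- Share negative = Φ(-z).
- Mean with negatives set to the limit = L + s[zΦ(z) + φ(z)].
- Mean with negatives dropped = L + s[z + φ(z)/Φ(z)].
- Mean with negatives coded 0 on the log scale = mean with negatives at the limit, minus L × share negative.

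**Worked case, 40% negative in CZ.**

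- CZ: z = 0.2533, Φ = 0.600, φ = 0.3863. Excess over the limit = 1.5 × (0.1520 + 0.3863) = 0.807.
- KSK: z = 0.2533 - 1.0/1.5 = -0.4133, Φ = 0.3397, φ = 0.3663, so 66% are negative. Excess = 1.5 × (-0.1404 + 0.3663) = 0.339.
- At the limit: 0.807 - 0.339 = 0.47.
- Dropped: 0.807/0.600 - 0.339/0.3397 = 1.35 - 1.00 = 0.35.

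Simulation (4,000 runs) gives 0.48 and 0.36; the gap of 0.01 is simulation error.

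**Worked case, 20% negative in CZ, coded 0.** The difference at the limit is 0.69 and the KSK share negative is 43%, so 0.69 + 2 × (0.43 - 0.20) = 1.15.

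**Simulated estimates of the true 1.0, with power in brackets.** With every value observed, power would be about 0.72.

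| CZ / KSK negative | Patients with a value (of 60) | Dropped | At limit | 0 on log scale | Rank test power | Tobit median |
|---|---|---|---|---|---|---|
| 5% / 16% | 54 | 0.72 (0.53) | 0.90 (0.71) | 1.13 (0.70) | 0.69 | not run |
| 20% / 43% | 41 | 0.49 (0.28) | 0.69 (0.65) | 1.15 (0.67) | 0.66 | 1.02 |
| 40% / 66% | 28 | 0.36 (0.14) | 0.48 (0.57) | 1.00 (0.62) | 0.60 | 0.99 |
| 60% / 82% | 17 | 0.25 (0.06) | 0.28 (0.45) | 0.73 (0.53) | 0.51 | 1.01 |
| 80% / 93% | 8 | 0.18 (0.02) | 0.12 (0.23) | 0.39 (0.34) | 0.33 | 1.05 |

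With no true difference, no t-test coding is biased and type I error stays at or below about 0.05.

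**Second model, on change from day 0.** Assumed: baseline mean 5 and SD 1.5, decline 0.35 log10 per day (SD 0.15), a further 0.10 per day under KSK, visit SD 0.7, limit 2. Ranges cover repeated simulation runs.

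- Day 7, true difference 0.70, about 38% v 51% negative: dropped 0.51 to 0.53 (power 23 to 26%); at the limit 0.39 (26 to 28%); Tobit adjusted for day 0, 0.67 to 0.70 (48%).
- Day 14, true difference 1.40, 76% v 89% negative: dropped 0.63 to 0.68 (6 to 9%); at the limit 0.24 to 0.27 (11 to 12%); Tobit 1.28 to 1.40 (36 to 42%).

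At day 7, ANCOVA with negatives at the limit has power 36% and estimates 0.38. About 10 of the 22 points gained over the t test at the limit thus come from baseline adjustment, which does not remove the bias.

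**The case against.** A reader might infer that the protocol discards the patients who clear the virus, or sets them to a floor, and that the treatment difference is therefore badly understated. The document does not support that reading.

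- **Coding.** No section says that negatives are dropped or floored. Such a rule is commonly left to the statistical analysis plan, which was not available, so its absence is no fault. What stands is the choice of test: no single-value coding lets a t test represent values known only to be below a limit.
- **Size and direction.** Neither is fixed. At 5% negative with values at the limit the loss is slight, and coding as 0 on the log scale overstates the difference at low shares.
- **Scale.** Table 5 names neither a log scale nor Ct. On raw copies a negative can be entered as 0 and nobody is lost. But power there is only 0.05 to 0.08 for shares of 5 to 80%, because of skew and not because of the negatives, so this is no workable way out.
- **Day 14.** The assumed mean loads are 5 - 14 × 0.35 = 0.1 and 5 - 14 × 0.45 = -1.3, both well below the limit of 2. The difference of 1.40 is an extrapolation into values that cannot be observed, and Tobit recovers it because the simulated data are close to normal. The day-14 figures deserve little weight.
- **Remedy.** A rank test or an analysis of clearance is also defensible. The rank test is not always stronger than the t test: in the second model its day-7 power is 22%, against 26 to 28% at the limit.
- **Consequence.** The trial is a pilot without a power claim, and false positives are not inflated. That limits the seriousness but does not rescue the estimate.

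**Conclusion.** The concern holds as a poor match between method and outcome. The protocol expects negative PCR results by day 7 or 14 and fixes a test that can use them only by omission or arbitrary coding. A real difference is then distorted, usually toward zero. Under the stated assumptions, a true 1.0 log10 is estimated at 0.90 down to 0.12 with negatives at the limit, and at 0.72 down to 0.18 with negatives dropped, as the CZ share negative rises from 5% to 80%. The share negative, SD and detection limit are all assumed, so these figures are a range and not a forecast. The change should be made, but the trial is not invalid without it: if the arms do not differ, the t test stays unbiased and keeps its error rate.

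**What to change.** In Table 5, replace the t test for viral load with a left-censored (Tobit) regression of log10 viral load on arm and the day-0 value. State that a negative sample counts as below the detection limit and never as missing. As a sensitivity analysis, show a rank test with all negatives tied at the lowest rank. Report the number undetectable per arm at days 7 and 14. If a separate statistical analysis plan exists, bring it into line.

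The cost is one table cell and a few lines of code. No new data are needed, since PCR is already scheduled on days 0, 7 and 14. There are small downsides. The model assumes normal errors on the log scale and becomes fragile when most values are censored, as may happen at day 14. Its likelihood-ratio test may be slightly liberal at 30 per arm (6.5 to 7% in 400 runs, 4 to 6% in another set), which is why the rank test belongs beside it. Part of its power gain comes from the baseline adjustment rather than from the handling of negatives.
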